### Interventions

The India and Tanzania trials will assess the non-inferiority of a low-dose calcium supplementation regimen (500 mg elemental calcium/day) as compared to the standard high-dose calcium supplementation regimen (1500 mg elemental calcium/day). The trial regimens will be taken by pregnant women from randomization to the time of delivery (no postnatal supplementation). The standard high-dose 1500 mg calcium supplementation regimen was selected to align with WHO recommendations [10]. The low-dose calcium supplementation regimen was selected to align with low-dose calcium supplementation regimens used in prior low-dose calcium trials [9]. Both randomized groups will take three regimen tablets per day to have identical pill burden in both randomized groups. The trial regimen is manufactured by Influx Healthcare (Maharashtra, India).

Women in both randomized groups will receive a regimen box containing a 35-day supply of trial regimen in blister packs. Each blister pack will contain a 7-day supply of trial regimen (7 × 3 tablets per blister pack) with columns indicating morning, midday, and evening tablets. A diagram of the regimen blister pack for each trial is presented in Additional file 2. Participants in both groups will be counseled to take one trial regimen tablet in the morning, one in the midday, and one in the evening with meals and to take iron-containing prenatal supplements provided as standard of care several hours apart from the calcium trial regimen.

Standard high-dose calcium group (1500 mg elemental calcium/day): Pregnant women will be provided and counseled to take three regimen tablets daily with each containing 500 mg elemental calcium as calcium carbonate supplements daily (total of 1500 mg elemental calcium). In India, daily vitamin D_3_ supplementation (250 IU) is recommended to be taken with calcium supplements and therefore each tablet in the standard high-dose calcium group will also contain 83.3 IU of vitamin D_3_ for a total of 250 IU vitamin D_3_ daily [14]. In Tanzania, the supplements in the standard high-dose calcium group will not contain vitamin D_3_.

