Low-dose calcium group (500 mg elemental calcium/day): pregnant women will be provided and counseled to take three regimen tablets each day with the first morning pill containing 500 mg elemental calcium as calcium carbonate, while the second (midday) and third (evening) tablets will be placebo supplements (total of 500 mg elemental calcium per day). The placebo tablets will be identical in all ways as compared to the calcium supplements (appearance, color, shape, size, weight, taste). In India, each of the three daily regimen tablets in the low-dose calcium group will also contain 83.3 IU of vitamin D_3_ for a total of 250 IU vitamin D_3_/day. Therefore, the daily vitamin D_3_ dose will be identical between standard high-dose and low-dose calcium groups in India. In Tanzania, the supplements in the low-dose calcium group will also not contain vitamin D_3_.

Multiple strategies will be used to improve adherence to interventions in India and Tanzania. At both sites, research staff will take a pill count at each study visit by counting the number of unconsumed tablets returned in the regimen blister packs. Study staff will counsel participants on taking the trial regimen and provide advice on overcoming barriers. At the India site, community health workers (accredited social health activists (ASHAs)) will also be engaged to promote regimen adherence during their routine home visits. At the Tanzania site, biweekly text message reminders for adherence and upcoming study visits will be sent. At both the India and Tanzania trial sites, reminder telephone calls will also be made prior participants’ scheduled visits by the research team and if the subject anticipates that she will not be able to attend the clinic visit or does not attend the clinic visit as planned, a home visit will be made by research staff. The research staff will provide the regimen, take pill counts, and conduct clinical assessments (including blood pressure and proteinuria) at home visits.

Participants may withdraw from the study at any time. In addition, study investigators or study physicians can decide that a participant should not continue to take the trial regimen or participate in the study if there are safety concerns or if continued participation does not appear in the best interest of the participant.

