We will also conduct a per-protocol analysis for preeclampsia and preterm birth. The per-protocol analysis for preeclampsia will include all participants who had > 75% adherence to the supplementation regimen based on pill count, had a pregnancy ≥ 20 weeks gestation, and had a delivery outcome assessed (excluding withdrawal and loss-to-follow-up in pregnancy). The per-protocol analysis for preterm birth will include all participants who had > 75% adherence to the supplementation regimen and a live birth. We will present relative risks and 90% confidence intervals for the per-protocol analyses but will not formally test non-inferiority.

We will use similar methods for analysis of secondary binomial maternal and infant outcomes (Table 2). We will present relative risks and 95% confidence intervals for secondary outcomes but will not formally test non-inferiority between randomized groups.

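### The per-protocol cut counts placebo tablets, so it guarantees more than 75% of assigned calcium in the high-dose arm but only more than 25% in the low-dose arm

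*Protocol article*

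**What the plan says.** All places are in the protocol article.

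- **Regimen (Interventions).** "Both randomized groups will take three regimen tablets per day to have identical pill burden in both randomized groups". High-dose women receive "three regimen tablets daily with each containing 500 mg elemental calcium". Low-dose women have the "first morning pill containing 500 mg elemental calcium as calcium carbonate", while "the second (midday) and third (evening) tablets will be placebo supplements".
- **Packaging and counting (Interventions).** Each blister pack is laid out "with columns indicating morning, midday, and evening tablets". Staff count the unused tablets that are returned at each visit. The text mentions neither a count by column nor any weighting of active against placebo tablets.
- **Per-protocol sets (Statistical methods).** The preeclampsia set requires more than "75% adherence to the supplementation regimen based on pill count", a pregnancy of at least 20 weeks and an assessed delivery outcome. The preterm birth set requires more than "75% adherence to the supplementation regimen and a live birth".
- **Role.** ITT is the primary approach and carries the non-inferiority test. Relative risks and 90% confidence intervals are reported "for the per-protocol analyses but will not formally test non-inferiority".

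**The concern.** A per-protocol analysis in a non-inferiority trial asks whether the result holds among women who received roughly what they were assigned. In the high-dose arm every tablet is active, so the tablet count measures calcium intake. In the low-dose arm two thirds of the count is placebo, so the same percentage says much less about calcium. The label *more than 75% adherent* therefore means different things in the two arms.

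The Discussion says that equal tablet numbers let the trials assess the biological effect of the calcium regimen. A set that serves that aim should reflect calcium received. The other planned sensitivity analyses (excluding pregnancy losses and withdrawals before 20 weeks; singletons only) do not concern adherence, so this is the only analysis that does. At stake is how clearly that supportive estimate can be read, not the primary conclusion.

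**Working it through.** The plan gives no size, power or intake figure for the per-protocol sets, so there is none to reproduce. Table 1 concerns the main tests and does not enter here.

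**Inputs** (Interventions; Statistical methods): three tablets a day in both arms; 500 mg per active tablet; active tablets 3 of 3 (high dose) and 1 of 3 (low dose); cut above 75% of tablets; 35-day box, so 35 × 3 = 105 tablets. The preterm birth criterion is assumed to use the same pill count.

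**High-dose arm.** Calcium share equals total share, so the cut guarantees more than 0.75 × 1,500 = 1,125 mg/day.

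**Low-dose arm.** Let *a* be the share of morning (active) tablets taken and *b* the share of placebo tablets. A woman enters if (a + 2b)/3 > 0.75.

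- With b = 1: a > 3 × 0.75 − 2 = 0.25, which is more than 0.25 × 500 = 125 mg/day.
- With a = 1: she is excluded if b ≤ (3 × 0.75 − 1)/2 = 0.625.

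**In whole tablets, per box.** 0.75 × 105 = 78.75, so 79 tablets are needed.

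- 70 placebo + 9 active = 79: included, with 9/35 = 25.7% of her calcium (about 129 mg/day).
- 35 active + 43 placebo = 78 (74.3%): excluded, with 100% of her calcium.

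**How often this might occur.** The documents give no adherence data, so these patterns are assumptions: beta-distributed *a* and *b* with parameters summing to 5, linked through correlated normal variables.

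| Assumed mean a / b, correlation | In low-dose set | Of these, ≤75% of calcium | Of these, ≤50% of calcium | Excluded among women with >75% of calcium |
|---|---|---|---|---|
| 0.80 / 0.80, 0.9 | 68.5% | 6.4% | 0.0% | 6.3% |
| 0.80 / 0.80, 0.7 | 68.8% | 11.3% | 0.1% | 10.9% |
| 0.90 / 0.70, 0.7 | 60.3% | 0.6% | 0.0% | 32.1% |
| 0.70 / 0.85, 0.7 | 69.6% | 35.9% | 1.6% | 2.7% |

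Intake near the 25% boundary is rare. Milder misclassification ranges from negligible to sizeable, depending on which tablets are missed.

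**Direction.** By pill count, a low-dose woman cannot exceed 500 mg/day of trial calcium and a high-dose woman in the set has more than 1,125 mg/day. Any two women in opposite arms of the set therefore differ by more than 1,125 − 500 = 625 mg/day. If calcium is effective in this range, keeping under-dosed low-dose women makes low dose look worse, which works against a non-inferiority finding.

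**Effect of also requiring the morning column above 75%.** The low-dose guarantee becomes more than 0.75 × 500 = 375 mg/day. The rule removes exactly the women in the third column, so the low-dose set becomes:

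- 68.5% × (1 − 0.064) = 64.1%
- 68.8% × (1 − 0.113) = 61.0%
- 60.3% × (1 − 0.006) = 59.9%
- 69.6% × (1 − 0.359) = 44.6%

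**The case against.** The case for the present rule is good, and most of it stands.

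- One total count applies the same behavioural criterion in both arms and needs no allocation codes, which suits blinded analysts. Counting only active tablets in the low-dose arm would lose both advantages.
- The adherence threat usually feared here is that missed high-dose tablets pull intake towards the low-dose regimen. The cut already guards against this by guaranteeing more than 1,125 mg/day.
- The 25% case needs every placebo taken and about three quarters of morning tablets missed, although women are counselled to take all three tablets alike.

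A reader might infer that the set is the only check on the ITT result, or that it can neither confirm nor challenge it. The documents do not support either. Two other sensitivity analyses are planned, and the set keeps a clear dose contrast with reported 90% intervals that can be compared with the margins. A reader might also infer that the rule favours a false non-inferiority claim, but under-dosing in the low-dose arm acts in the opposite direction. Testing formally on ITT alone is a stated choice, and a joint ITT and per-protocol requirement would be a preference rather than a correction.

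What the defence does not remove is the unequal guarantee: more than 25% against more than 75% of assigned calcium under one label.

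**Conclusion.** The point holds as a limited flaw in a supportive analysis. As written, the cut guarantees more than 75% of assigned calcium in the high-dose arm and only more than 25% in the low-dose arm, and it can exclude a woman with full low-dose intake. The arithmetic rests only on the stated regimen and threshold, read as a count of all tablets. If the unshown SAP already counts by column, the point falls away.

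How many women are affected is unknown. Under the assumed patterns, 0.6% to 36% of the low-dose set took 75% or less of their calcium and 0% to 1.6% took half or less, while 3% to 32% of women above 75% were excluded. These ranges illustrate sensitivity to the assumptions and are not estimates from the documents. The consequence is a blurred per-protocol estimate. The ITT test is unaffected.

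**What to change.** Require both the morning-column count and the total count to exceed 75%, in both arms and for both primary outcomes. The returned blister packs already separate the columns. At the least, add this as a second per-protocol set among women with column counts, and fix the definition before unblinding. The rule is identical across arms, needs no allocation codes, and raises the guaranteed low-dose intake from more than 125 to more than 375 mg/day.

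Costs and limits:

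- **Set size.** The low-dose set shrinks by 0.6% to 36% of its members under the patterns above. The loss is large only if morning tablets are the ones most often missed.
- **Data.** Enrolment began in November 2018 (India) and March 2019 (Tanzania), so column counts may be missing for completed pregnancies. The article does not show whether they were recorded.
- **What it leaves.** Women who took all their calcium but missed placebo tablets remain excluded. Removing that exclusion would need an arm-specific rule, with loss of the blind and different selection in the two arms.

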## Statistical methods

The India and Tanzania trials will be analyzed independently; however, the outcome definitions and statistical methods will be the same for both trials. An intent-to-treat (ITT) analysis will be the primary approach for all analyses and one-sided tests for non-inferiority with a type I error rate of 0.05 will be used. The ITT analysis for preeclampsia will include all randomized women and the preterm birth ITT analysis will include all livebirths. A complete case analysis will be used in the primary analyses.

For preeclampsia, we will use a log-binomial model with a fixed effect for study clinic to account for the stratified randomization scheme to produce relative risk estimates for the preeclampsia outcome for the low-dose as compared to the standard high-dose calcium supplementation group. The upper bound of the 90% confidence interval of the relative risk for preeclampsia will be compared with the prespecified noninferiority margin to assess non-inferiority. The primary analysis for preeclampsia will be among all randomized participants. We will conduct a sensitivity analysis for preeclampsia excluding pregnancy losses and participants who withdraw before 20 weeks gestation. In addition, we will also construct Kaplan–Meier curves with gestational age as the time metric to visualize the incidence of preeclampsia between randomized groups. We will present relative risks and 90% confidence intervals but will not formally test non-inferiority for any preeclampsia sensitivity analyses.

For preterm birth, a generalized estimating equation (GEE) analysis with the log link, a fixed effect for study clinic and a compound symmetry working correlation matrix to account for correlations due to multiple gestation will be used to construct relative risks for preterm birth among live births between randomized groups. The 90% confidence intervals of the relative risk will be compared with the prespecified non-inferiority margin to assess non-inferiority. We will conduct a sensitivity analysis for preterm birth among singleton pregnancies and will present relative risks and 90% confidence intervals but will not formally test non-inferiority.

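### The per-protocol preeclampsia set selects on what happens after the event, so some confirmed cases are removed although their outcome is known

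*Protocol article*

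**What the plan says.** The protocol article, under Statistical methods, sets three conditions for the per-protocol preeclampsia analysis: "> 75% adherence to the supplementation regimen based on pill count", a pregnancy of at least 20 weeks, and that the woman "had a delivery outcome assessed (excluding withdrawal and loss-to-follow-up in pregnancy". The article gives no period over which adherence is counted and no exception for a woman whose preeclampsia is already confirmed.

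Other sections bear on how these conditions work:

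- Interventions: "The trial regimens will be taken by pregnant women from randomization to the time of delivery". Pill counts are taken at each study visit from unconsumed tablets returned in the blister packs, and tablets are supplied in 35-day boxes.
- Interventions: "study investigators or study physicians can decide that a participant should not continue to take the trial regimen or participate in the study", so stopping tablets is possible without leaving the study.
- Pregnancy study visits and Outcomes: blood pressure and urine protein are checked every 4 weeks, and a blinded committee confirms each preeclampsia event.
- Statistical methods, on the primary analysis: "The ITT analysis for preeclampsia will include all randomized women", with complete-case handling. On the per-protocol analysis: "We will present relative risks and 90% confidence intervals for the per-protocol analyses but will not formally test non-inferiority".

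**The concern.** Preeclampsia may be established weeks before delivery, but two of the entry conditions go on being judged after that date.

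The first is the delivery-outcome condition. A woman with a confirmed event who later withdraws or is lost while still pregnant fails it, so a known event leaves the analysis. A woman who dies undelivered would also fail it on a literal reading, although death is not named.

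The second is adherence. If the count runs to delivery, tablets not taken after the event lower a woman's score. A case taken off tablets early can then be classed as non-adherent because of her outcome.

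The sensitivity analysis for preeclampsia in the same section limits its withdrawal exclusion to before 20 weeks. The per-protocol rule has no such limit.

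At stake is how the per-protocol relative risk and 90% confidence interval can be read. In a non-inferiority trial they will be set beside the intention-to-treat result, whether or not they are formally tested.

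**Working it through.** **The plan's own figures.** The article gives no figure for the per-protocol set. The nearest is the Table 1 power for preeclampsia, which reproduces and is not in dispute. Inputs from Sample size: 5,500 per arm less 10% = 4,950, risk 1.5%, margin 1.54, one-sided 0.05. The margin on the difference scale is 0.015 x 0.54 = 0.0081. The standard error is sqrt(2 x 0.015 x 0.985 / 4,950) = 0.00244. Then z = 0.0081/0.00244 - 1.645 = 1.67, which is 95.3%, as stated. I use 4,950 per arm below. The real per-protocol set would be smaller.

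**Delivery-outcome route.** No arithmetic is needed. Event confirmed, then withdrawal or loss before delivery, means no entry under the rule as written.

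**Adherence route (assumes a count to delivery).** Cumulative adherence = prior adherence x (stop week - randomization week) / (delivery week - randomization week). The dates are illustrative.

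| Randomized | Stop | Delivery | Prior adherence | Cumulative | In set? |
|---|---|---|---|---|---|
| 14 | 30 | 37 | 100% | 16/23 = 69.6% | no |
| 14 | 33 | 36 | 85% | 0.85 x 19/22 = 73.4% | no |
| 16 | 36 | 37 | 100% | 20/21 = 95.2% | yes |

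The time off tablets that brings adherence down to 75% is L x (1 - 0.75/a), where L is weeks from randomization to delivery and a is prior adherence. For randomization at 12 to 19 weeks and delivery at 34 to 39 weeks, L runs from 15 to 27:

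- a = 100%: 3.8 to 6.8 weeks
- a = 90%: 2.5 to 4.5 weeks
- a = 80%: 0.9 to 1.7 weeks

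**Effect on the relative risk (removal shares assumed).** If only cases are removed, the observed relative risk is close to the true value x (share of cases kept, low dose) / (share kept, high dose). The high-dose arm would have about 74 events at 1.5% and 248 at 5% among 4,950.

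| Cases removed, high / low dose | True 1.30 becomes |
|---|---|
| 20% / 20% | 1.30 |
| 10% / 20% | 1.30 x 0.80/0.90 = 1.16 |
| 20% / 10% | 1.30 x 0.90/0.80 = 1.46 |

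At 3% high-dose risk and a true 1.30, the upper 90% limit is 1.55 with no removal. It becomes 1.41 with 10% / 20% removal and 1.77 with 20% / 10%. An imbalance of that size could move the limit across 1.54 in either direction.

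**The case against.** The strongest reply is that nothing decisive rests on this set. Intention-to-treat in all randomized women decides non-inferiority, and the per-protocol result is presented without a test. That stands and limits the importance of the point. A reader might infer that the per-protocol analysis is the plan's check on the primary result, but the article never gives it that role.

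Several other inferences go further than the text:

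- *Stopping tablets after preeclampsia removes a woman.* It does so only if her cumulative adherence ends at 75% or below, and the count to delivery is an assumption. If adherence were tablets taken over tablets dispensed, a woman given no further boxes after a stop would lose little. The discretion to stop for safety does not mention preeclampsia.
- *Women who move away are lost.* Under Labor and delivery study visit, those who deliver elsewhere are reached by phone and through records.
- *Risk must be understated in both arms.* Leavers without an event are excluded too. On that route, risk falls only if cases leave more often than non-cases, and the article gives no rates.
- *The bias favours low dose.* More cases in one arm does not mean a larger share of cases removed. Allocation is blinded, equal shares leave the relative risk unchanged, and the opposite imbalance raises it.
- *The preterm set has the same fault.* Its outcome occurs at delivery, when dosing ends, and no matching defect is shown.

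The remedy also has a selection cost. It keeps leavers with an event and drops leavers without one, and it gives cases a shorter adherence window. Suppose 3% risk, 10% leaving regardless of outcome, and half of the leavers' events confirmed first. The present rule gives 2.7/90 = 3.0%, and the revised rule gives 2.85/90.15 = 3.16%. That cost is real but small, and it applies in both arms.

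**Conclusion.** The concern holds in a limited form. By its own wording, the rule excludes women with confirmed preeclampsia who withdraw or are lost before delivery. If adherence is counted to delivery, it also excludes early cases who are off tablets long enough to finish at or below 75%. That takes about 4 to 7 weeks for a fully adherent woman and less with lower prior adherence. Late events followed soon by delivery are not affected.

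The effect on the relative risk cannot be sized from the article. It needs a different share of cases removed in each arm, and neither the shares nor the direction is known. The shift from 1.30 to about 1.16 or 1.46 shows what a 10% versus 20% imbalance would do; it is not an estimate. The analysis is supportive, so the primary conclusion is not at risk. The wording is still worth correcting, because the estimate and its interval will be read next to the primary result.

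**What to change.** For preeclampsia only, replace the adherence and delivery-outcome conditions, including the bracketed exclusion of withdrawal and loss, with: *more than 75% adherence from randomization to the earlier of the confirmed preeclampsia event or the end of pregnancy; and either confirmed preeclampsia or a delivery outcome assessed*. Keep the 20-week condition as it is. For each arm, report how many confirmed cases are in the set only because of this rule, so that any imbalance is visible.

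This changes analysis wording only. Pill counts are already taken at each visit, and the planned Kaplan-Meier curves by gestational age already need event timing. Keeping a confirmed case who later leaves is also consistent with the complete-case intention-to-treat analysis, where her outcome is known.

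The costs are one event-dependent date to derive per woman and slightly higher absolute risks in both arms, because event-free leavers remain excluded. The preterm-birth set needs no change on this ground.
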